### Economic Evaluation

The aim of the economic evaluation is to determine the 6 and 12 month costs of use of health services associated with the intervention from a societal perspective, where all costs are assessed regardless of who bears them. A societal perspective is recommended for studies relevant to societal policy decisions [112].

#### Data Analyses

We will conduct cost-effectiveness analysis (CEA) on person level cost and effect data using net benefit regression [117,118]. The dependent variable for the net benefit regression in this analysis will be *nb *which equals *effect *· $ - *cost *where *effect *= improvement in CES-D, $ = the monetary value of each unit of *effect *and *cost *= the costs accrued over the study period. Different values of $ will be used to explore how sensitive the results are to assumptions about $. In the base case scenario, the dependent variable *nb *will be modelled as a function of the patient variables described above and a stochastic error term (ε). We will estimate the coefficient β_0 _in the regression nb = β_0 _+ **β_x _x **+ ε where **x **is a vector of patient variables that have been centred on their means, **β_x _**is a vector of their respective coefficient estimates, ε is a stochastic error term and β_0 _is an estimate of cost-effectiveness. When β_0 _> 0, the intervention is deemed to be cost-effective since the value of the extra benefit is greater than the extra cost [117]. Net benefit regressions will be run for a variety of $ values and then the probability of cost-effectiveness will be plotted against values for $ on a cost-effectiveness acceptability curve [119]. In this way, the research findings will allow different decision makers to use different preferred values of $. By placing the CEA in a regression framework, we will be able to use a wide variety of regression tools while exploring key patient characteristics and using regression model diagnostic tools [120].

### Process Evaluation

The purpose of the process evaluation is to determine the feasibility and acceptability of the intervention. Assessment of feasibility determines whether the intervention can be successfully implemented to establish actual exposure to the intervention as it was intended, and to examine which components of the intervention were successful and which ones were not [121]. Assessment of acceptability determines the suitability of the intervention from the perspective of the study participants and the intervention providers [121]. Table 2 provides an overview of all process variables and measures used in the study.

#### Variables and Measures

Assessment of the *feasibility of the intervention *will include: a) the reach of the intervention, defined as the proportion of the intended target population that actually participated in the intervention, b) the dose delivered, defined as the number and duration of the home visits and case conferences during the 6-month intervention, and c) the level of fidelity to treatment (the extent to which the RNs and PSWs adhere to the components of the intervention). We are keeping a record of all clients who meet the eligibility criteria for the study to determine the recruitment rate and assess the reach of the intervention. Alphanumeric characteristics (age, gender, medical diagnosis, referral source) of the clients who are assessed as eligible for the study but refuse to participate will be collected at baseline to assess the representativeness of the sample. Data on the dose of the intervention and the RNs' and PSWs' actual adherence to the intervention will be gathered by the RNs and PSWs themselves by means of prospective self-reports. The RNs and PSWs will use the monthly visit and case conference record and the depression care booklet after each case conference to record which components of the intervention were applied. Each item will be scored as a done/not done binary variable (see Table 3 for the key intervention features that will be scored) [122,123].

**Table 3 T3:** Fidelity Scale

Intervention Components	Data Source	Yes	No
**Staffing and Supervision**			

RNs and PSWs receive standardized training	Attendance record		

RNs and PSWs meet with investigators on a monthly basis	Attendance record		

**Follow-Up**			

In-home visits by trained RN at least once per month for 6 months	Monthly visit records		

In-home visits by trained PSW at least once per month for 6 months	Monthly visit records		

**Standardized Screening Tools**			

Depressive symptoms monitored once per month using the GDS-15 [92]	Depression care booklet		

Cognitive status monitored at baseline, 3 and 6 months using the SMMSE [81]	Depression care booklet		

Presence of delirium monitored at baseline, 3 and 6 months using the CAM [135]	Depression care booklet		

Anxiety monitored at baseline, 3 and 6 months using the GAD-7 [107]	Depression care booklet		

Nutritional status monitored at baseline, 3 and 6 months using the SCREEN II [137]	Depression care booklet		

Caregiver stress monitored at baseline, 3 and 6 months using the Modified CSI [136]	Depression care booklet		

Behavioural problems due to cognitive problems and mood disorders monitored once per month by PSW using the GIP-28 [93]	Depression care booklet		

Problem-solving ability monitored at baseline, 3 and 6 months using the problem-solving test [84]	Depression care booklet		

**Depression Education**			

Received education about depression and treatment options using printed educational materials	Depression care booklet		

**Interprofessional Care**			

Participants are discussed at a case conference at least once per month for 6 months	Monthly case conference record		

Referred to health and social services, as needed	Depression care booklet		

Interprofessional client service plan developed	Client service plan		

Evidence of communication between RN, PCP and other IP providers	Depression care booklet Client service plan		

**Treatment Planning and Delivery**			

Problem-solving therapy delivered at least once per month for 6 months	Depression care booklet		

Social and behavioural activation provided by RN and PSW	Depression care booklet		

Antidepressant medication management is provided using evidence-based guidelines	Depression care booklet Client service plan		

Assessment of the *acceptability of the intervention *will include: a) the level of engagement to the intervention (the number of participants who receive at least one home visit over the 6-month period), b) perceptions of the intervention by study participants as measured by semi-structured interviews, and c) perceptions of the intervention by the intervention providers as measured by focus group interviews. Data on the perceptions of the intervention by study participants will be determined through the use of five open-ended questions during the final 12-month interview: "Which aspects of the nurse-led program were most helpful to you?" "Which aspects of the nurse-led program were the least helpful to you?" "Which aspects of the nurse-led program have you continued to use?" "Which aspects of the nurse-led program haven't you continued to use?" "Would you recommend this program to other people?" The RNs and PSWs will be invited to a focus group interview at 6 and 18 months following initiation of the intervention to discuss their perceptions of the intervention, including the intervention components they perceive to be most and least helpful and to identify barriers and facilitators to implementation: "What aspects of the nurse-led intervention have worked well for clients and their families, home care providers, and the organization and system?" "What kinds of challenges have there been with respect to implementing the nurse-led intervention for clients and their families, home care providers, and the organization and system?"

#### Data Analyses

Study participants will be compared with clients who are assessed as eligible for the study but refuse to participate on their alphanumeric characteristics at baseline using independent t-tests for continuous variables and chi square for categorical variables. Descriptive analysis of the dose of the intervention will be expressed as the mean (standard deviation [SD]) and range (minimum-maximum) number of home visits and case conferences. Data on the RNs' and PSWs' actual adherence to the intervention will be categorized as the proportion of times each component of the intervention was implemented. Content analysis of the older home care clients' responses to the open-ended questions will be used to analyse the qualitative data. Participant answers will be sorted into categories and themes. Descriptive analysis will be performed for the frequency of the answers for each question.

The focus groups will be digitally recorded and transcribed verbatim by an experienced transcriptionist and checked for accuracy by a Research Assistant. Qualitative data will be managed using N-VIVO 8 software. Three of the investigators ([name]) will systematically review all transcripts and inductively generate a list of codes by hand describing themes. The codes will be grouped into themes (a higher conceptual level) and sub-themes. The investigators will use a constant comparison approach to interpret data. This will involve reviewing coded data that supported themes and continually referring to previously coded sections for comparison. By comparing and contrasting the coded data, sub-themes, themes, interrelationships and patterns will be revealed. Differences of opinion will be discussed until agreement is reached.

## Discussion

In this paper we describe the background, design and methods of an ongoing prospective study of the effectiveness of a nurse-led, IP mental health promotion intervention aimed at older home care clients with depressive symptoms. This research has two important innovative aspects. First, this is the first study that investigates the effectiveness of a 6-month nurse-led, IP mental health promotion intervention among this population. Studies on the effectiveness of nurse-led mental health promotion interventions in home care have involved short-term screening and referral for depression rather than ongoing treatment and regular follow-up care over a 6-month period. Second, it is the first study to investigate the effectiveness of such an intervention among at-risk seniors with depressive symptoms using PSS, as opposed to the general population of seniors using home care services. Such individuals are considerably frailer than the general population of seniors receiving home care services and are often excluded from community-based studies. Thus, this study will make an important contribution by providing knowledge of the effectiveness of a nurse-led mental health promotion intervention among a more vulnerable group of older home care clients than recruited in previous studies. Stratifying individuals into different levels of risk is important from a clinical and economic perspective because those at greatest risk are more likely to benefit from preventive efforts and can be targeted specifically [17,37].

Our primary hypothesis is that a nurse-led IP mental health intervention offered to older home care clients with depressive symptoms, will result in a reduction in the severity of depressive symptoms, and will pay for itself because the cost of the health care resources related to the intervention will be offset by a lower cost of use of other expensive health care resources. For example, in Canada, hospital costs constitute the largest component of health care expenditures for depression, at approximately $3.8 billion dollars per year [10]. An older person with depression has a 25% chance of being hospitalized within one year, with the average acute care cost of treatment of about $21,800 per person with depression [124]. Based on previous research, we expect to decrease the average use of acute hospitalization by 17% in the 250 participants receiving the nurse-led approach [69], which translates into a cost savings of 43 people × $21,800 = $937,400 in the same year due to prevention of acute hospitalization for depression; this by itself should create enough savings to pay for the intervention. However, to determine if our hypothesis is correct, we will examine costs expended as well as costs averted by all sectors of society (e.g., beyond acute care hospital costs), to reflect a societal perspective.

If our hypothesis is correct, we will conclude that a nurse-led IP mental health promotion intervention, proactively provided to older home care clients with depressive symptoms, reduces depressive symptoms and enhances health-related quality of life at no more cost to society as a whole, thus making the intervention highly feasible given its clinical benefits. The results of this project will provide evidence for the feasibility, acceptability, and effectiveness of an innovative model of service delivery that has the potential to significantly improve the quality of life of older home care clients with depressive symptoms and reduce demand for health services achieved by: improving the recognition and management of depressive symptoms; linking home care, primary healthcare, and specialized mental health services; facilitating effective IP collaboration and teamwork; facilitating timely access to depression-related care and services; promoting adoption of best practice guideline recommendations for depression care; providing regular follow-up care and treatment over 6 months; developing and implementing standardized prevention, education, and screening protocols; and expanding health care provider knowledge and skills in depression care, chronic disease management, and IP collaboration. The results of this research will add to the accumulating evidence that early, proactive, and comprehensive care for older adults with chronic needs is both more effective and no more expensive in a system of national health insurance than providing services on a limited, reactive, and piecemeal basis [70,78,91,113,114].

The results will also provide information about the processes and strategies that foster: effective IP collaboration, use of best practice depression guideline recommendations, and integration and coordination of home care, primary healthcare, and depression-related services for this population. The knowledge gained from this research will be made available to decision-makers and clinicians to inform policy and practice related to the allocation and delivery of services for the prevention, early identification, and management of depression among older home care clients. These findings will have application in other home care and community-based practice settings.

Many older adults using PSS are "at-risk" for depression, but the rate of depression and depression risk factors have not been previously investigated in this population. Our results will provide information on the prevalence, determinants and costs of depressive symptoms among older home care clients using PSS. On the basis of previous research among a general population of older home care clients [1,27,70], we expect that depression will be highly prevalent in this population and associated with poor health-related quality of life, low social support, and higher use of health services. We also hypothesize that depression in this population will be largely untreated or undertreated [1]. The two step screening and recruitment process may identify seniors who would not in the normal course of events have received any treatment for their depression, thus highlighting the importance of incorporating screening into routine clinical practice. Improving understanding of the prevalence of depression will help to raise awareness of the important role of home care in recognizing, managing, and reducing depression in this population. Knowledge about risk factors for depression among older adults using PSS, can be used to guide the allocation of scarce home care resources to those most likely to benefit from preventive efforts.

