The present study builds on this work by developing and testing a mental health promotion intervention involving proactive follow-up by nurse (RN) care managers working collaboratively with the PSW, the home care case manager, the client's primary care physician (PCP), and other IP home care providers (e.g., occupational therapy, physiotherapy, social work), among at-risk seniors with depressive symptoms using PSS, as opposed to the general population of seniors using home care services. The specific objective of the study is to evaluate the feasibility, acceptability, and effectiveness of a 6-month nurse-led IP mental health promotion intervention aimed at older home care clients with depressive symptoms using PSS. Our primary hypothesis is that a nurse-led IP mental health promotion intervention, delivered to older home care clients with depressive symptoms, will result in a reduction in the severity of depressive symptoms in this population. Further, we hypothesize that the nurse-led intervention will result in a reduction in depression risk factors and will pay for itself by reducing the use of expensive healthcare resources. These study findings will inform the role of nurses within the IP home care team in the management of depression and will generate lessons learned that are relevant to other home care settings. Given the increasing numbers of those over 65 years of age [19] and the increasing demand for PSS [20], this collaborative nurse-led strategy may provide a feasible, acceptable and effective means for improving the quality of life of older home care clients by improving the prevention, early recognition, and management of depression. We also discuss the issues and challenges involved in designing a practical, transferable and sustainable nurse-led strategy in home care.

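### The planned conclusion of no extra cost to society has no criterion: the only written economic rule, net benefit above zero, addresses cost-effectiveness and cannot show cost neutrality

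*Protocol article*

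**What the plan says.** **The hypothesis.** The Discussion's primary hypothesis combines symptom reduction with the statement that the programme "will pay for itself because the cost of the health care resources related to the intervention will be offset by a lower cost of use" elsewhere in the health system. The Background is different: there the primary hypothesis is symptom severity alone, and cost comes afterwards: "Further, we hypothesize that the nurse-led intervention will result in a reduction in depression risk factors and will pay for itself".

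**The conclusion.** The Discussion fixes in advance what will be concluded if the hypothesis is correct: the programme "reduces depressive symptoms and enhances health-related quality of life at no more cost to society as a whole".

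**The rule.** Economic Evaluation, Data Analyses, defines net benefit as effect times a dollar value per unit, minus cost. Effect is improvement in CES-D, and cost is "the costs accrued over the study period". When the regression intercept is above zero, "the intervention is deemed to be cost-effective since the value of the extra benefit is greater than the extra cost". The dollar value is left open: "Net benefit regressions will be run for a variety of $ values", and an acceptability curve will be drawn.

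**Other cost plans.** The Abstract says changes in cost will be assessed. The Economic Evaluation plans 6- and 12-month costs that include delivery of the intervention. The Discussion says costs expended and averted will be examined to judge the hypothesis. The limitations paragraph concedes that there is no comparison group.

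**The concern.** A statement of no extra cost concerns cost alone: the mean change in cost is at or below zero, or below a stated margin. To support it, a plan needs an estimate of that change and a rule for how far its upper bound may reach.

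The written rule concerns something else. It trades health gain against cost at an assumed exchange rate, so a programme that raises spending can satisfy it if the gain is valued highly enough. The other cost plans describe what will be measured, but none says what result would justify the conclusion.

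The Discussion intends the findings for decision-makers who allocate services. Worth its cost at a given value per CES-D point and no more cost are different messages for a payer, and the article's rule can support only the first.

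**Working it through.** **1. The plan's own cost figure.** The Discussion projects a 17% reduction in hospitalisation among 250 participants: 0.17 × 250 = 42.5, rounded to 43, and 43 × $21,800 = $937,400. The product reproduces. It is a projection behind the hypothesis, not a criterion for judging the data.

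**2. The rule with cost read as extra cost.** Let E be the mean CES-D improvement, V the dollar value per point and D the mean extra cost per person. The intercept is E × V − D, which is positive whenever D < E × V. E = 3.5 is the difference used in the sample size section.

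| Value per point (V) | Largest extra cost that still passes (3.5 × V) |
|---|---|
| $0 | $0 |
| $100 | $350 |
| $500 | $1,750 |
| $1,000 | $3,500 |

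Read the other way, an extra cost D passes once V exceeds D / 3.5. For D = $1,000 that is $1,000 / 3.5 = $286. Only at V = 0 does the rule reduce to a statement about cost, and the plan does not tie its conclusion to that value.

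**3. The rule read literally.** Cost is defined as accrued cost, with no baseline subtracted. At V = 0 the intercept is then minus mean total cost, which is negative for any programme whose participants use services, whether spending rose or fell. At V > 0 it passes once V exceeds total cost / 3.5. For illustration, use hospital cost alone from the Discussion's figures (25% yearly risk, $21,800 per person), with the yearly risk converted to 6 months by assuming a constant rate:

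- 6-month risk = 1 − √0.75 = 0.134
- mean 6-month hospital cost = 0.134 × $21,800 ≈ $2,921
- with $1,000 added, ≈ $3,921
- break-even V = $3,921 / 3.5 ≈ $1,120

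The literal rule is harder to pass ($1,120 against $286), but it still does not test whether cost changed.

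**4. Whether a plain significance test would fill the gap.** The article's general rule is a two-sided test at 0.05. Suppose it were applied to a before-after cost change. The spread below is an assumption: hospital cost only, one fixed cost per hospitalised person, correlation 0 between periods, normal approximation.

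- SD of 6-month cost = $21,800 × √(0.134 × 0.866) ≈ $7,426
- SD of the before-after change = $7,426 × √2 ≈ $10,501
- completers = 250 × 0.80 = 200
- SE = $10,501 / √200 ≈ $743
- true increase of $1,000 = 1,000 / 743 ≈ 1.35 SE
- probability of a non-significant result ≈ 0.73

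With correlation 0.5 between periods, the SD of the change falls to $7,426, the SE to about $525, and the probability to about 0.52. In both cases a $1,000 increase per person goes undetected more often than not. The half-width of the 95% interval is 1.96 × $743 ≈ $1,455 at correlation 0 and 1.96 × $525 ≈ $1,029 at 0.5.

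**The case against.** **The article does not say that positive net benefit means no extra cost.** Correct. It labels the rule cost-effective and says separately that costs expended and averted will be examined. A reader might infer that the authors will report a passing net benefit as cost neutrality, or will treat a non-significant cost change as neutrality. Neither inference has support in the text. What stands is narrower: a conclusion is announced, and no stated rule can support it.

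**The analysis plan or full protocol may supply the criterion.** An article may leave the list of dollar values and the interval method to a fuller document. A value of zero is not excluded, because no values are listed. But this point rests on two statements within the article, a decision rule and a conclusion, that answer different questions. Including zero in the list would not repair that while cost is defined as accrued cost.

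**Cost is not the primary question.** A reader of the Discussion might infer that half of the primary hypothesis goes untested. The documents do not settle this: the Background makes cost a further hypothesis, and the primary outcome and analysis are CES-D only. The two statements should be reconciled. The conclusion on cost is announced under either.

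**The $286 break-even is not the rule as written.** It applies only if cost means extra cost. Under the accrued definition the threshold is higher, which is why both readings are shown.

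**Conclusion.** The point holds as a mismatch between the stated economic rule and the stated conclusion. Net benefit above zero can support a claim of cost-effectiveness at a named value per CES-D point; it cannot support a claim of no extra cost. This follows from the formula under either reading of cost and needs no assumed figures.

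The sizes are illustrations. The $286 threshold rests on a 3.5-point gain and on cost meaning extra cost. The 73% miss rate (52% at correlation 0.5) rests on the Discussion's hospital figures, a constant rate over the year, hospital cost only and 200 completers. The true spread of total societal cost is not given in the article.

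A reader might also infer that a before-after cost bound below zero would prove that the programme pays for itself. It would not: without a comparison group it describes a change over time, not a difference from usual care.

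**What to change.** 1. In the Economic Evaluation data analyses, define a per-person cost change: cost in the 6-month follow-up period, including delivery of the intervention, minus cost in the 6 months before baseline, both from the HSSUI. Report its mean with a bootstrap 95% confidence interval.
2. State that no extra cost, or paying for itself, will be concluded only if the upper bound is at or below zero or a dollar margin fixed in advance. Otherwise, reword the Discussion's hypothesis and conclusion to cost-effective at a stated dollar value per CES-D point.
3. State that positive net benefit at a value above zero supports only that second wording, and that a non-significant cost change is not evidence of no extra cost.
4. State that the result is a before-after change and not a difference against usual care.
5. Reconcile the Background and the Discussion on whether cost belongs to the primary hypothesis.

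The cost is one added estimate from data already planned, plus rewording. The downside is that the interval may be wide: with the half-width of about $1,455 above, the observed saving would have to be at least that large per person for the upper bound to reach zero. The claim becomes harder to make.
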